## Abstract

**Background:**

Low- and middle-income countries are facing an increase in the incidence of acute pancreatitis (AP)—characterized by rapid onset, fast progression, high rate of severity, and high mortality. Progression of AP into severe AP (SAP) results in a series of complications such as organ dysfunction, local abscesses, pseudocysts, and necrosis. Although the treatment of AP is primarily supportive, including fluid resuscitation and organ support, there is still a lack of consensus on the optimal management regimen for fluid therapy, and strategies to promote gastrointestinal recovery remain limited. As no effective intervention measure has yet been developed, supportive therapy remains the primary approach for the early treatment of AP. DaXianXiong decoction is a widely used traditional Chinese medicine formulation; however, limited research has been conducted on its clinical efficacy.

**Objective:**

This study aims to evaluate the efficacy and safety of DaXianXiong decoction in preventing AP from progressing to SAP, assessing its impact on SAP incidence, clinical severity scores, inflammation markers, and gastrointestinal function, and providing evidence for AP management.

**Methods:**

This study is a randomized, double-blind, placebo-controlled, single-center clinical trial. The primary outcomes will include the incidence of SAP, modified computed tomography severity index score, APACHE II (Acute Physiology and Chronic Health Evaluation II) score, modified Marshall score, and levels of the inflammation factor. The secondary outcomes will include the effect of the gastrointestinal dysfunction treatment. Evaluations will be conducted at baseline; 24 hours after the intervention; and on days 3, 7, and 28 after the intervention in both groups. A total of 60 eligible patients will be randomly allocated in a 1:1 ratio to the intervention group and the control group. Both groups will receive standard Western medical treatment for pancreatitis. The intervention group will additionally receive DaXianXiong decoction, while the control group will receive a placebo similar to the decoction.

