### Outcome Measures

The outcome measures will be determined at various time points throughout the study, including baseline (T0, before treatment), 24 hours after the final treatment (T1, end point 1), 3 days after the final treatment (T2, end point 2), 7 days after the final treatment (T3, end point 3), and 28 days after the final treatment (T4, final end point). The data collection and assessment schedule are listed in Table 2.

**Table 2 table2:** The data collection and assessment schedule.

Assessments		Study period				Follow-up		
		Enrollment and allocation (T0)	Intervention (48 hours)	Primary end point (T1)	T2		T3	T4

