### Primary Outcomes

The primary outcome of this study is the incidence of SAP, which will be calculated using the following formula:

SAP incidence (%) = (number of SAP cases/total number of patients) × 100%

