## Results

This study has been funded by the Performance Incentive Project of Scientific Research Institutions in Chongqing. The trial was registered in April 2024, and data analysis is expected to be completed by April 2025. The recruitment for the trial commenced in December 2023. The data has been collected and is being analyzed. The study results will be presented at both national and international conferences and published in peer-reviewed journals.

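### The Abstract names five primary outcomes and the Methods name one, and the definition of that one gives no time point

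*Protocol article*

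**What the plan says.** **Which outcome.** The Methods paragraph of the Abstract begins "The primary outcomes will include the incidence of SAP, modified computed tomography severity index score", adds the APACHE II score, and ends with "modified Marshall score, and levels of the inflammation factor". It then says: "The secondary outcomes will include the effect of the gastrointestinal dysfunction treatment". That makes five primary outcomes, with gastrointestinal effect as the only secondary outcome named.

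The Primary Outcomes section of the main text says: "The primary outcome of this study is the incidence of SAP". The modified CT severity index, APACHE II, modified Marshall score and inflammation factor levels each have their own subsection under Secondary Outcomes.

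**Which time.** The formula under Primary Outcomes divides cases by patients and mentions no visit. Table 2 ticks severe pancreatitis incidence at T1, T2, T3 and T4. One column of that table is headed "Primary end point (T1"). The Outcome Measures text describes the same visit as "24 hours after the final treatment (T1, end point 1") and the last visit as "28 days after the final treatment (T4, final end point").

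**Which threshold.** Data Analysis sets a two-sided P ≤.05 and does not distinguish primary from other tests.

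**Status.** The Results section reports: "The data has been collected and is being analyzed".

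**The concern.** The primary outcome decides what the trial can claim. On the Methods list, success means fewer patients developing severe pancreatitis, which is the stated objective. On the Abstract's list, a difference in a CT score, a physiological score or a cytokine could also be reported as a primary result, although it would not show that progression had been prevented.

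Nothing else in the article settles the matter. The sample size was based on the time for blood amylase to normalise, which is on neither list. Because the data are already in, readers of the final report will look to this article for what was fixed beforehand, and it gives them two answers.

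The missing time point matters for the same reason. Incidence 24 hours after the last dose and incidence by day 28 are different quantities.

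**Working it through.** **1. Inputs from the article**
- Primary outcomes in the Abstract: 5. In the Methods: 1.
- Inflammation markers in Table 2: C-reactive protein, IL-1, IL-4, IL-6, IL-8, IL-10 and TNF-α, so 7.
- Variables if each marker is counted separately: 4 + 7 = 11.
- Visits after baseline: 4.
- Significance level: .05, two-sided, for every test.

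The article gives no family-wise error figure to reproduce. The Sample Size section states α = .05.

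**2. Assumptions, not in the article**
- Any one significant primary outcome would support a primary claim.
- There is no treatment effect on any outcome.
- The test statistics are approximately normal with a common correlation ρ. The article gives no correlations, so ρ runs from 0 to .7.

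**3. Formulas**

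For *m* independent tests:
- at least one false positive in either direction: 1 − .95^*m*
- at least one favouring the decoction: 1 − .975^*m*

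| *m* | Either direction | Favouring the decoction |
|---|---|---|
| 1 | 5.0% | 2.5% |
| 5 | 1 − .95^5 = 22.6% | 1 − .975^5 = 11.9% |
| 11 | 1 − .95^11 = 43.1% | 1 − .975^11 = 24.3% |

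For correlated tests the same quantities are P(max\|Z\| > 1.96) and P(max Z > 1.96), with equally correlated normal statistics:

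| *m* | ρ | Either direction | Favouring the decoction |
|---|---|---|---|
| 5 | .3 | 20.9% | 10.5% |
| 5 | .5 | 18.3% | 9.2% |
| 5 | .7 | 14.8% | 7.4% |
| 11 | .3 | 37.5% | 19.1% |
| 11 | .5 | 30.4% | 15.2% |
| 11 | .7 | 22.3% | 11.2% |

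The ranges are therefore:
- five outcomes at one visit: about 15–23% in either direction, 7–12% favouring the decoction
- eleven variables at one visit: about 22–43% and 11–24%.

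**4. Upper bound.** Eleven variables at four visits make 11 × 4 = 44 tests. If independent, 1 − .95^44 = 89.5%. This needs the Abstract's list, seven markers each carrying a claim, every visit eligible and no correlation, all at once. It is not an estimate of the trial's error rate.

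**5. After alignment.** One outcome at one stated time is one test, with an error rate of 5% two-sided and 2.5% favouring the decoction.

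**The case against.** The best case on the other side accepts the five-against-one mismatch and disputes what is built on it.

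- **T1 against T4.** A reader might infer that the article names two rival primary times. It does not. The text numbers the visits as end points 1, 2, 3 and final, so "final" most naturally means the last in the series, and only T1 is labelled primary anywhere. Read with Table 2, the Methods could mean one test, at T1. This objection stands. What remains is that the sentence defining the primary outcome gives no time and the text does not repeat the table's label.
- **Dozens of chances to win.** A reader might also infer that success can be declared on any of 44 tests with a 90% chance of error. The article does not support this. The Abstract treats inflammation factor levels as one item, and the main text gives several of the interleukins an exploratory purpose. Two-sided rates also count results favouring placebo. This objection stands, and it is why both directions are shown above.
- **No decision rule.** The article does not say that one of the five outcomes is enough. If all five had to succeed, error would not be inflated. This is correct, and the figures are conditional on the any-one reading.
- **No multiplicity adjustment.** Such a rule is commonly left to a statistical analysis plan, which is not shown here, so its absence is not a fault. It does not rescue the article, because a multiplicity rule needs a known primary set and two sets are given.
- **Choice after seeing results.** The Results section reports that analysis is under way. It does not say that anyone has seen results by arm, and no such inference should be drawn.

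**Conclusion.** The point holds as an internal contradiction: five primary outcomes in the Abstract, one in the Methods, with the other four listed there as secondary. The omission of a time point from the primary outcome is a lesser ambiguity.

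The excess false-positive risk applies only if any one of the Abstract's outcomes could carry a primary claim at .05. With five outcomes, the chance of a false win for the decoction is then roughly three to five times that of a single test (7.4/2.5 ≈ 3.0; 11.9/2.5 ≈ 4.8). Counting seven markers separately raises it further. The contradiction itself needs none of these assumptions. It should be corrected before results are reported, because it decides what the trial can conclude.

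**What to change.** 1. Change the Abstract to match the Primary Outcomes section, with incidence of severe acute pancreatitis as the sole primary outcome.
2. State in the Primary Outcomes section and in Table 2 the single time point that was fixed before unblinding, and give the date on which it was fixed. If none was fixed, say so. A preferred visit should not be chosen now: with data collected, moving to or away from T1 would itself be a late choice of end point.
3. Label the modified CT severity index, APACHE II, modified Marshall score and inflammation markers as secondary throughout, with no confirmatory claim.
4. Disclose any departure from the registered primary outcome. The registry entry is not among the documents, so agreement with it cannot be checked here.

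The cost is a text edit. The real concession is that success can no longer be claimed on a score or marker alone.

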**Results:**

This study has been funded by the Performance Incentive Project of Scientific Research Institutions in Chongqing. The trial was registered in April 2024, and data analysis is expected to be completed by April 2025. The study results will be presented at both national and international conferences and published in peer-reviewed journals.

**Conclusions:**

This trial will help us assess the effectiveness and safety of DaXianXiong decoction in patients with AP and provide clinical evidence on the efficacy and safety of DaXianXiong decoction in preventing the progression of AP to SAP. By evaluating its impact, the findings will contribute to the understanding of DaXianXiong decoction as an adjunct therapy in AP management and may offer a novel complementary treatment strategy for AP, potentially improving patient outcomes and reducing complications.

**Trial Registration:**

Chinese Clinical Trial Registry ChiCTR2300076885; https://www.chictr.org.cn/showproj.html?proj=207084

**International Registered Report Identifier (IRRID):**

DERR1-10.2196/67392

## Introduction

Acute pancreatitis (AP) is a common yet potentially fatal inflammatory disorder of the pancreas, characterized by severe abdominal pain, multi-organ dysfunction, and pancreatic necrosis. The global incidence of AP is approximately 30-40 cases per 100,000 people, with over 2000 fatalities annually [1]. Severe AP (SAP), which involves persistent organ failure lasting ≥48 hours, is the most life-threatening form of AP, with a mortality rate of 20%-40% despite significant advancements in treatment [2-4]. Approximately 20% of patients with AP progress to SAP, which is associated with severe complications such as organ failure, infections, and increased health care costs [1,5].

The pathophysiology of AP is characterized by premature activation of trypsin within the pancreatic acinar cells, triggering pancreatic autodigestion and leading to a systemic inflammatory response. This response results in systemic inflammatory response syndrome, which can progress to multi-organ dysfunction syndrome [6,7]. Although the treatment of AP is mainly supportive, including fluid resuscitation and organ support, there remains a lack of consensus on the optimal management protocols for fluid therapy [8,9], and strategies to promote gastrointestinal recovery remain limited [10].

In addition to conventional Western treatments, Chinese herbal medicines have gained attention for their potential in managing AP. Chinese herbal medicines are known for their ability to target multiple biological pathways involved in inflammation, immune response, and organ protection, offering a broader approach compared to single-target Western therapies [11,12]. DaXianXiong decoction, a traditional herbal formula used in China for over 30 years, has been reported to improve gastrointestinal symptoms and modulate inflammation. However, its clinical efficacy in preventing the progression of AP to SAP has not been conclusively demonstrated due to the lack of robust randomized controlled trials [12-14].

In light of these challenges, there is an urgent need for high-quality studies to evaluate the efficacy and safety of DaXianXiong decoction in the treatment of AP. This study aims to assess the potential of DaXianXiong decoction in preventing the progression of AP to SAP, reducing inflammatory markers, improving gastrointestinal function, and assessing safety and complications.

## Methods

### Trial Design

This is a single-center, randomized, double-blind, placebo-controlled study. It adheres to the guidelines mentioned in the SPIRIT (Standard Protocol Items: Recommendations for Interventional Trials) statement (Multimedia Appendix 1).

During the trial, all eligible patients will be randomly assigned to either the intervention group or the placebo group. Both groups will receive the standard treatment for AP. A detailed workflow depicting the study process is presented in Figure 1.

**Figure 1 figure1:**
[figure not shown]
Workflow.

### Study Population

Patients will be enrolled from the intensive care unit in Chongqing Traditional Chinese Medicine Hospital, a grade III level A hospital in China.

### Recruitment of Patients

The study group will be recruiting and allocating the patients. Eligible patients who are willing to participate in the trial will be provided with an informed consent form with details of the study objectives, procedures, and potential risks (Multimedia Appendix 2).

### Patient and Public Involvement

Our research will not include any design, implementation, or reporting from patients or the public.

### Inclusion Criteria

We will select patients based on the following inclusion criteria:

Presence of AP as confirmed using the revised Atlanta classification [15]Aged 18-75 yearsTime of illness onset under 24 hours

### Exclusion Criteria

We will use the following exclusion criteria:

Patients with severe diseases affecting vital organs, such as liver dysfunction, heart failure, and malignant tumorsPatients participating in another study within 3 months of enrollmentThose with known allergies to any of the prescribed medicinesPregnant or lactating women

### Withdrawal Cases

Patients can withdraw from the study at any point without any repercussions. If a patient discontinues the intervention or decides to participate in another study, they will no longer be included in the present study. However, even when a patient withdraws from the study, the data collected up to that point will be retained and included in the analysis, unless specifically requested otherwise. The withdrawal and noncompliance of patients will also be documented. Incomplete data will be addressed based on the withdrawal rate. If the rate is <5%-10%, we will perform data cleaning. If the withdrawal rate exceeds 10%, the missing data will be managed through imputation, intention-to-treat analysis, and sensitivity analysis.

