### Management of Dropout Cases

All patients who provide informed consent and meet the eligibility criteria for enrollment in this randomized controlled trial, irrespective of the timing or reasons for their withdrawal later, will be categorized as dropouts if they are lost to follow-up. However, patients who discontinued the treatment regimen because of complete symptom remission will not be considered dropouts. The investigators will comprehensively document the reasons for each dropout in the case report form. Real-world circumstances, including adverse events (AEs), will be accounted for during the statistical analysis. In addition, we will carefully record and preserve the data about all enrolled patients who will receive the assigned investigational medications, regardless of their withdrawal status, for observation purposes and to be used as a data archive and for the intention-to-treat analysis.

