In the event of a serious AE or allergic reaction caused by the research medication, the principal investigator will open the emergency envelope and discontinue the trial for that patient. Details of the event and unblinding will be recorded in the case report form, and the patient will receive appropriate treatment. The relevant departments and ethics committees will be promptly notified within 24 hours.

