### Adverse Events

All AEs will be carefully documented, including the start and end dates, severity, relationship to the study drug, and patients’ continued involvement in the study. Any serious AE will be promptly reported to the research ethics committee within 24 hours. If an AE occurs, the patient will be advised to discontinue the use of the decoction, and the researchers will evaluate whether it is related to the formulation. Emergency safety measures will be implemented, if necessary, to ensure the well-being of patients. Persistence of AEs will be monitored until their resolution. Please note that AEs are not the complications clearly related to AP, such as acute respiratory distress syndrome, abdominal compartment syndrome, and acute kidney injury.

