### Data Management and Monitoring

An independent data and safety monitoring board will be established to monitor the conduct and safety of the study. Two of our research team members will be responsible for updating our clinical trial–related information on the Chinese Clinical Trial Registry website and for making sure that no data are missed. However, if this becomes inevitable, we will use various processing methods to handle the issue. We will also perform a sensitivity analysis of the test results simultaneously.

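### Patients who stop study drug are taken out of the study before severe acute pancreatitis is first assessed, so their primary outcome may be missing

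*Protocol article*

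**What the plan says.** All references are to the protocol article. SAP here means severe acute pancreatitis.

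- **Withdrawal Cases:** "If a patient discontinues the intervention or decides to participate in another study, they will no longer be included in the present study". Data collected before the patient leaves are kept and analysed unless the patient asks otherwise. Imputation, intention-to-treat and sensitivity analysis are brought in if withdrawal exceeds 10%; at lower rates the section plans data cleaning.
- **Interventions, on serious adverse events:** for a serious adverse event or allergic reaction caused by the study drug, "the principal investigator will open the emergency envelope and discontinue the trial for that patient".
- **Adverse Events:** "If an AE occurs, the patient will be advised to discontinue the use of the decoction". Complications clearly related to acute pancreatitis are not counted as adverse events.
- **Outcome Measures and Table 2:** the first assessment after baseline is "24 hours after the final treatment (T1, end point 1"). SAP is ticked at T1, T2, T3 and T4, and neither at baseline nor during the 48-hour intervention.
- **Introduction:** "Severe AP (SAP), which involves persistent organ failure lasting ≥48 hours". **Inclusion Criteria:** patients enter less than 24 hours after onset.
- **Primary Outcomes:** SAP incidence is "number of SAP cases/total number of patients".
- **Management of Dropout Cases:** data on enrolled patients who receive study medication are recorded and preserved "regardless of their withdrawal status, for observation purposes and to be used as a data archive and for the intention-to-treat analysis".
- **Data Management and Monitoring:** "We will also perform a sensitivity analysis of the test results simultaneously".

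**The concern.** Withdrawal Cases treats stopping the drug in the same way as joining another study: both end participation. In a trial with a 48-hour course and outcome visits only afterwards, a patient who stops during the course leaves before any scheduled SAP assessment. Keeping the data collected so far then keeps mainly baseline data.

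The reasons for stopping are not neutral. An adverse event leads to advice to stop, and a drug-caused serious event or allergic reaction ends the trial for that patient. If the decoction causes more such events than placebo, SAP statuses are lost unevenly between the arms, and the comparison is no longer protected by randomisation. The primary outcome is defined over the total number of patients, and this rule can leave some of them without a numerator value.

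**Working it through.** The plan gives no expected number of stops, so it has no figure of its own to reproduce. The check is one of timing, followed by a bound.

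**Step 1: when SAP is first assessed.** The course lasts 48 hours (Interventions) and T1 is 24 hours after the final treatment. For a full course, T1 falls about 48 + 24 = 72 hours after the start. Nothing earlier is scheduled.

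**Step 2: when SAP can first be established.** It needs organ failure for at least 48 hours. Entry is less than 24 hours after onset. Assuming that organ failure does not precede onset of the illness, the earliest time is more than 48 − 24 = 24 hours after entry.

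**Step 3: what the retained data can hold.**
- Stop within about 24 hours of entry: the data retained up to that point cannot yet establish SAP.
- Stop later within the course: SAP could already be present if organ failure began before or near entry, but no assessment is scheduled, so the status may or may not be on record.
- Stop after T1: at least one SAP assessment exists. This case is not affected in the same way.

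**Step 4: whether other sections supply the status.**
- Management of Dropout Cases preserves data for intention-to-treat whatever the withdrawal status. This conflicts with the removal rule, but the section does not say that stoppers are assessed for SAP at T1 to T4.
- Withdrawal Cases makes intention-to-treat and imputation conditional on withdrawal above 10%. With 60 patients, 10% is 6, so up to 6 withdrawals do not trigger them.
- The sensitivity analysis under Data Management and Monitoring has no threshold, but it cannot recover a status that was never assessed.

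**Step 5: how much a missing status matters.** There are 30 patients per arm (Sample Size). With *k* statuses missing in total, in whichever arm, counting each as SAP or as no SAP moves the arm difference over a range of *k*/30:
- *k* = 1: 1/30 = 3.3 percentage points
- *k* = 3: 3/30 = 10.0 points
- *k* = 6: 6/30 = 20.0 points

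For scale, take 20% SAP in each arm, the progression rate given in the Introduction. The standard error of the difference is √(2 × 0.2 × 0.8 / 30) = 0.103, or 10.3 points. The values of *k* are assumptions, and the ranges are worst-case bounds, not estimates of bias.

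**The case against.** The strongest reply is that Management of Dropout Cases undertakes to record, and not only to archive, data regardless of withdrawal status, for observation and for intention-to-treat. The same section calls a withdrawn patient a dropout only if lost to follow-up, so withdrawal and loss are treated as different things. Adverse Events records whether the patient stays involved in the study, which suggests that an event with advice to stop does not automatically end participation. T1 could also be counted from the last dose actually taken. Finally, these are intensive-care patients at one hospital, so the status can probably be recovered.

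Much of this stands. It shows that the protocol contradicts itself and does not uniformly abandon stoppers. It does not settle the matter: no section says that stoppers are assessed for SAP, a visit timed from the last dose does not help a patient who has already left, and no section commits to using hospital records for this purpose.

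A reader might infer that every patient who stops during the course necessarily lacks the primary outcome. The documents do not support that; Steps 2 and 3 show it only for stops within about 24 hours of entry. A reader might also infer that one lost status would decide the significance test. That would need event counts, which the protocol does not give, and would depend on choosing counts close to the .05 boundary. It would also depend on dropping stoppers from a denominator that Primary Outcomes defines as all patients, and on a Pearson test with small expected counts.

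**Conclusion.** The point holds as a conflict of rules that puts the primary outcome at risk. Withdrawal Cases and the serious-event paragraph under Interventions do not separate stopping study drug from leaving the study, and SAP is scheduled only after the course. SAP status may therefore be missing for patients who stop early.

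Each missing status leaves 3.3 points of uncertainty in the arm difference, against a standard error of 10.3 points at 20% per arm. One is small on that scale; three are about as large as the standard error. The true size is unknown because the number of stops is not stated. The direction of any bias is also unknown: events clearly due to pancreatitis are excluded from the adverse events that prompt stopping, so those who stop need not be at higher or lower risk of SAP. The timing conclusion rests on the 48-hour definition in the Introduction and on the entry window. The point should be settled before analysis, but it does not show that the result is biased.

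**What to change.** The Results section says that data have been collected and are being analysed, so the remedy belongs before the analysis is completed:

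1. List every stop of study drug by arm, reason and time.
2. Retrieve SAP status through T4 from hospital records for these patients, where consent allows.
3. Make the primary analysis all randomised patients in their assigned arm, whatever the withdrawal rate, with the denominator given under Primary Outcomes.
4. For any status still missing, report the SAP difference with it counted as SAP and again as no SAP.
5. State under Withdrawal Cases and in the serious-event paragraph of Interventions that stopping study drug is not leaving the trial, in line with Management of Dropout Cases.

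The cost is record retrieval at one hospital for the patients who stopped, one extra sensitivity table and short wording changes. No further patients are needed. Visits already missed cannot be restored, so some statuses may have to stay as bounds.
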